## Abstract

**Background:**

Robot-assisted therapy (RAT) and virtual reality (VR)-based neuromotor rehabilitation have shown promising evidence in terms of patient’s neuromotor recovery, so far. However, still little is known on the perceived experience of use of robotic and VR devices and the related psychosocial impact. The present study outlines a study protocol aiming to investigate the biopsychosocial effects and the experience of use of robotic and non-immersive VR devices in patients undergoing neuromotor rehabilitation.

**Methods:**

Adopting a prospective, two-arm, non-randomized study design, patients with different neuromotor diseases (i.e., acquired brain injury, Parkinson’s Disease, and total knee/hip arthroplasty) undergoing rehabilitation will be included. In a real-world clinical setting, short- (4 weeks) and long-term (6 months) changes in multiple patient’s health domains will be investigated, including the functional status (i.e., motor functioning, ADLs, risk of falls), cognitive functioning (i.e., attention and executive functions), physical and mental health-related quality of life (HRQoL), and the psychological status (i.e., anxiety and depression, quality of life satisfaction). At post-intervention, the overall rehabilitation experience, the psychosocial impact of the robotic and VR devices will be assessed, and technology perceived usability and experience of use will be evaluated through a mixed-methods approach, including both patients’ and physiotherapists’ perspectives. Repeated measures within-between interaction effects will be estimated, and association analyses will be performed to explore the inter-relationships among the variables investigated. Data collection is currently ongoing.

**Implications:**

The biopsychosocial framework adopted will contribute to expanding the perspective on patient’s recovery within the technology-based rehabilitation field beyond motor improvement. Moreover, the investigation of devices experience of use and usability will provide further insight into technology deployment in neuromotor rehabilitation programs, thereby maximising therapy engagement and effectiveness.

**Trial registration:**

ClinicalTrials.gov ID: NCT05399043.

## 1. Background

Over the past two decades, due to the aging population and the consequent increase in related diseases, serious healthcare challenges have emerged in most countries. This has generated the need for urgent solutions, including the implementation of interdisciplinary and innovative approaches along with technology-enabled smart healthcare strategies [1]. Contextually, the field of neuromotor rehabilitation has shown increasing interest in the introduction of robotic and virtual reality (VR) technologies given their multipurpose application to the patient recovery process [2, 3].

Robot-assisted therapy (RAT) has reported promising evidence so far, showing several advantages such as the possibility to provide repetitive, intensive, and task-oriented rehabilitation activities, as well as the opportunity to implement a smaller workforce, optimized exercise, and real-time quantitative motor impairment assessment and monitoring. Furthermore, the use of robotic devices has benefited from more complex and customized interventions, by managing the parameters that allow for the personalization of the recovery program based on patient characteristics, and by increasing the amount and quality of the treatment that can be administered [4]. Essentially, robotic devices have been applied to the rehabilitation process according to the principles of motor learning and neuroplasticity with the aim of better maximizing afferent input from peripheral joints and supply task-specific stimulation to the central nervous system so as to promote functional recovery of both the upper and lower limbs. For the former, the RAT consists in the execution of task-specific exercises with different levels of intensity and technology-based assistance promoting motor relearning of motor function, including arm and/or extremity range of motion, strength, and functional flexibility. For the lower limbs, the robot-assisted gait training (RAGT) has been widely implemented to target the regaining and the improvement of patient’s mobility, walking ability, and balance. For this purpose, different types of robotic devices (i.e., exoskeletons, end-effectors, soft-robots) have so far been implemented to target diverse chronic and complex diseases (of a traumatic, vascular or neurodegenerative nature) like stroke [5, 6], traumatic brain injury (TBI) and spinal cord injury (SCI) [7, 8], multiple sclerosis (MS) [9, 10], and Parkinson’s disease (PD) [11, 12], reporting evidence in favor of their feasibility and an improvement in patient autonomy in the activities of daily living (ADLs) and health-related quality of life (HRQoL). Moreover, prior research has also observed, beyond motor improvement, the psychological impact of implementing this technology, reporting for example significant post-intervention changes in patients’ depression and anxiety symptoms along with increased well-being [13, 14]. Despite the significance of these findings, studies including psychological factors as primary outcomes are still scant. Further research is needed on the effects of RAT adopting a psychosocial perspective, especially considering the well-known importance of the perception of disability in chronic neurological populations.

Likewise, VR technology has been shown to be a promising tool to improve rehabilitation outcomes. When various technical devices (e.g., head-mounted displays, desktop computers, motion capture and tracking systems, motion-sensing gloves) are implemented, it can deliver, through different levels of immersion, realistic experiences by the creation of and interaction with virtual environments (VEs) closely resembling everyday environments [15]. To date, a wide range of studies have tested and demonstrated the efficacy, for example, of VR-based treadmill training for lower extremities to reduce risk of falls, improve gait and balance [16] or of exercises in reaching and grasping virtual objects for upper extremities to increase arm and manual movement, dexterity, and coordination [17]. Moreover, commercially available serious game platforms (e.g., Nintendo Wii, Microsoft Kinect) have been effectively implemented to combine rehabilitation with the possibility to play games and perform various activities [18, 19]. Exercises through video games (i.e., exergame) have gained increased interest as they provide several advantages when compared to the conventional ones, including the motivation to practice through an interactive and attractive way, the possibility to train motor and cognitive skills performing dual tasks, and the shift of the focus to the outcome of the movement, displayed in the game, from the movement itself. Overall, the efficiency of VR technology may be firstly explained by its peculiarity to provide realistic, meaningful, and repetitive experiences delivered through specific tasks whose difficulty and complexity can be adapted according to each patient’s needs and characteristics [20]. Secondly, VR systems can also supply real-time and goal-directed feedback, which are considered key components facilitating quick self-correction and accommodating motor relearning [21, 22]. Therefore, significant improvements in motor impairment have so far been observed across pathologies. Nevertheless, as VR-based interventions are increasingly used, mixed results are reported in the literature. On the one hand, this heterogeneity is mainly due to the large number of technological platforms implemented, which implies a possible moderation effect of the VR technology-related variables (e.g., level of immersion, customization of the systems). On the other hand, it may be influenced by the characteristics of the population included (e.g., age, clinical diagnosis, disease severity) [3]. In general, the multimodal and multisensory stimulation as well as the possibility of personalization offered by VR have been shown to have the potential to increase patient engagement throughout rehabilitation programs, ultimately improving treatment compliance [23, 24]. Beside this advantage, this stimulation and complexity have been shown to be determinant in obtaining significant improvements in cognitive outcomes (e.g., memory, dual tasking, and visual attention) and secondarily in psychological functioning (e.g., anxiety reduction, higher well-being, and increased use of coping strategies) [25].

Consistent promising evidence has also been reported in the studies coupling VR to RAT. A recent study describing the effects of adopting this therapeutic approach has for example evidenced a significant improvement in HRQoL in terms of perceived mental and physical state, and in different cognitive domains, like cognitive flexibility and shifting abilities, selective attention and visual search [26]. Again, another work highlighted the positive impact of combining the two technologies showing significant changes in patient’s functionality, mobility, static and dynamic balance, and in problem-solving abilities [27]. Overall, the integration of VR in RATs has so far showed encouraging results. Even though robots are usually well accepted by patients, RAT may be perceived as poor motivating. Adding VR may overcome this limit as it was shown to augment the motivation to endure practice and to strengthen performance awareness, as well as to stimulate visual, tactile and auditory input, ultimately inducing, at synaptic level, deep cortical and subcortical changes that are central for motor relearning [28].

Ensuring adequate patient engagement and adherence to treatment represents another challenge to maximize therapy efficacy and success. Accordingly, the introduction of technological devices in rehabilitation programs has raised the issue of device usability and the related experience of use, with the idea that the more positively the technology is perceived and accepted, the stronger the patient’s motivation and satisfaction with the program and, thus, the more effective the therapy [29]. Usability refers to a patient’s perception and ability to use a device to achieve goals effectively, efficiently, and satisfactorily [30]. As a result, factors like device acceptability, usefulness, ease-of-use, and learnability are particularly important. These factors, however, do not always sufficiently explain the complexity of the experience of use. To better develop and expand the concept of device use, further aspects that embrace the full subjective user experience need to be considered too. Of these, socio-cognitive and experiential factors (e.g., emotions, expectations, motivation, satisfaction) may play a pivotal role in determining rehabilitation outcomes. For instance, the degree of a perceived sense of presence or the intensity of the adverse effects related to the exposure to VEs may deeply impact the quality of therapy delivery and, as a result, treatment outcomes, likewise the perceived safety and level of comfort in relation to the use of a robotic device [31, 32]. For the reasons above, exploring these indicators should be addressed, taking into account patients’ perspectives. In particular, when aiming to understand a patient’s perception and attitude toward the use of a device, it is likewise essential to consider the context in which it is used. In most cases, the implementation of technology during the rehabilitation program is necessarily supported and mediated by a therapist, whose expectations and views may be transferred to the patient [33, 34]. Accordingly, the social influence exerted by healthcare professionals represents an additional factor that should be considered as a possible determinant of the quality of patients’ experience of use.

Although the literature has already shown promising evidence in favor of the application of robotics and VR to rehabilitation programs, this research field is relatively recent. Therefore, beside the need for further studies corroborating the potential of this technology in terms of efficacy, more effort is needed to understand the related multidimensional impact across clinical populations by considering the centrality of factors like perceived HRQoL, and psychological and cognitive functioning. Accordingly, recent evidence has highlighted the adoption of a holistic approach in the field of technology-based neurorehabilitation as a still open challenge, where multiple patient’s health domains and their complementarity should be considered beyond motor improvement [27, 35, 36]. Likewise, other recent studies encouraged research on this topic to include formal evaluations with respect to the technology characteristics, especially to how these are perceived by the users, in order to maximise their functionality and the consequent effectiveness [37, 38]. Following this line, future research should therefore not only address the wider effects of technology implementation in rehabilitation programs, thereby providing clearer evidence on its efficacy and effectiveness, but it should also focus on the experiential factors and the usability issues related to the technology use, facilitating the related scaling-up process.

Based on the background described, it must be overall acknowledged that the wider impact of technology-based rehabilitation on patient’s non-motor outcomes has so far insufficiently investigated and that a consensus on technology formal evaluation procedures within recovery programs still lacks. Deeper investigation and clearer empirical evidence on this topic are therefore required. Accordingly, this paper aims to describe a study protocol called “Perception of High Technology in Rehabilitation: a prospective real-life Study on usability, effectiveness, and health-related quality of life” (PHTinRehab Study), whose main purpose is to explore, in a real-world clinical setting, the experience of use and the biopsychosocial effectiveness of robotics and VR devices in patients undergoing neuromotor rehabilitation. More specifically, the aims are:

to explore pre- post-treatment differences and long-term effects concerning: patients’ HRQoL, anxiety and depression symptoms, cognitive functioning, and functional status;to measure patients’ perceived experience of the rehabilitation program, as well as the perceived psychosocial impact and experience of using the robotic and VR devices (user experience and device usability);to observe the differences on technology evaluation, in relation to the pathology, disease severity, and type of device implemented;to extend the evaluation of the device perceived usability to the therapists and explore to what extent this is associated to patients’ perception of device usability and overall rehabilitation experience.

These aims present crucial implications for clinical practice and research. The evidence on short- and long-term biopsychosocial effectiveness of technology not only may help to discuss more deeply the impact of RAT and VR on motor improvement, but it would also add knowledge to the effects on patient’s psychological profile, ultimately expanding the perspective on patient recovery. Moreover, exploring patients’ perception of their technology-based rehabilitation program would provide crucial information on how the experience of using the technology devices throughout the recovery may differ depending on the pathology and disease severity. In a personalized medicine perspective, this would help future clinical practice and research to provide validated rehabilitation pathways that are tailored on patients’ needs and characteristics. Moreover, eliciting technology strengths and limitations from the therapists’ perspective would allow to collect informative data from a professional point of view and, thus, provide helpful indications for future devices development or adaptation, ultimately facilitating optimized technology deployment to neuromotor recovery programs.

## 2. Materials and methods

The protocol here described was registered in a public clinical trial registry (ClinicalTrials.gov Identifier: NCT05399043) and was developed following SPIRIT guidelines (http://www.spirit-statement.org/) and checklist [39]. Further details on SPIRIT schedule of enrolment, intervention, and assessment are provided in Fig 1.

**Fig 1 pone.0282925.g001:**
[figure not shown]
SPIRIT schedule of enrolment, interventions, and assessment.

### 2.1 Design, participants and procedures

The protocol has a prospective, two-arm, open-label, non-randomized study design (Fig 2). In a real-world clinical setting, patients will be consecutively enrolled according to the following eligibility criteria: 18 years of age or older; diagnosis of acquired brain injury (ABI; e.g., TBI, stroke), Parkinson’s Disease (PD) or orthopaedic disease (i.e., total hip/knee arthroplasty) requiring rehabilitation intervention; absence of a severe clinical condition (i.e., chronic heart failure at class IV according to the New York Heart Association classification—NYHA-IV, ischemic heart disease at class IV according to the Canadian Cardiovascular Society classification—CCS-IV, neoplastic diseases, acute respiratory diseases); no severe cognitive impairment (screened with the Montreal Cognitive Assessment–MoCA ≤ 15.5) [40]; no language disorders (e.g., aphasia); absence of severe mental health condition or psychiatric disorder (evaluated according to the Diagnostic and Statistical Manual of Mental Disorders—DSM-V) potentially compromising participation in the study; absence or withdrawal of the informed consent to participate.

**Fig 2 pone.0282925.g002:**
[figure not shown]
Study protocol flow chart. MBI, Modified Barthel Index; MFS, Morse Falls Scale; FIM, Functional Independence Measure; TUG, Timed Up & Go test; GPE, Global Perceived Effect; BADL, Basic Activities of Daily Living; IADL, Instrumental Activities of Daily Living; MoCA, Montreal Cognitive Assessment; SDMT, Symbol Digit Modalities Test; TMT, Trail Making Test; FAB, Frontal Assessment Battery; T-MoCA, Telephone Montreal Cognitive Assessment; EQ-VAS, Euro-QoL-VAS; SF-12, Short Form Health Survey-12; SAT-P, Satisfaction Profile; GAD-7, Generalized Anxiety Disorder-7; PHQ, Patient Health Questionnaire; CCRQ, Client-centred Rehabilitation Questionnaire; PIADS, Psychosocial Impact of Assistive Device Scale; SUS, System Usability Scale; ExTR, Experience in Technology-based Rehabilitation Schedule.

At hospital admission (or after clinical stabilization), patients will be screened according to the criteria described above by a panel consisting of physical and rehabilitation medicine specialists and researchers. Those considered eligible will undergo a multidimensional baseline evaluation including the functional status (i.e., disability, autonomy in the ADLs, risk of falls), cognitive functioning (i.e., attention, executive functions, reaction times, phonemic fluency), HRQoL, and psychological characteristics (i.e., quality of life satisfaction, anxiety and depression symptoms). After the intervention (4 weeks), patients will undergo the same evaluation battery to estimate pre- post-treatment differences and their rehabilitation experiences will be assessed. Participants will be divided into two subgroups, depending on their rehabilitation program. The first group will include patients who underwent conventional treatment exclusively, while the second group will be composed of those who participated in both conventional and RAT or VR-based rehabilitation. The latter, at post-intervention, will be further asked to evaluate the experience of use of the devices and the perceived usability (through a mixed-method approach), as well as the related perceived psychosocial impact. Technology evaluation will be also extended to the therapists involved in the rehabilitation programs. These will undergo mixed-method evaluation (i.e., questionnaire and semi-structured interview) aiming to collect data on the perceived usability of devices from the healthcare professional’s point of view. In conclusion, at six months following the rehabilitation program, all patients will be contacted by telephone and asked to provide information concerning their perceived functional status, level of autonomy in the ADLs, perceived HRQoL, and anxiety and depression symptoms.

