### 2.2 Intervention and technological devices description

All patients will receive conventional treatment consisting of two daily one-hour sessions over 4 weeks, including traditional rehabilitation activities like range of motion exercises (passive, active assisted and active), progressive resistive exercises, balance and strength training, and aerobic conditioning. For the patients additionally participating in the RAT or VR-based rehabilitation, part of the duration of the whole treatment will be dedicated to the use of the devices, resulting in the same amount of rehabilitation for all participants. According to the technological device implemented (i.e., RAT or VR-based treatment), the intervention procedures and the related eligibility to participate will be checked according to the technology-specific guidelines and recommendations as appropriate [41–43]. The intervention will be delivered following the routine multidisciplinary clinical practice of the Institution where the study will be conducted [44]. Specifically, for each patient, the clinical care pathway will be based on the integration of the International Classification of Diseases (ICD) and the International Classification of Functioning Disability and Health (ICF) models as recommended by the WHO framework [45]. Therefore, adopting a biopsychosocial approach, the rehabilitation procedures will be adapted according to the patient’s medical diagnosis, disability severity, and rehabilitation objectives in favor of an individualized rehabilitation project and program. Therefore, if necessary, patients may undergo parallel rehabilitation activities that will involve different healthcare professionals (i.e., occupational therapists, speech therapists, psychologists).

Technology-based rehabilitation will be delivered through the following exoskeleton or non-immersive VR devices.

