### 2.3 Data collection

Following preliminary collection of the socio-demographic (i.e., age, gender, living conditions, marital status, occupation, caregiver identification, and education) and clinical (i.e., BMI, primary diagnosis, comorbidities, health-related risk factors, and COVID-19-related anamnesis) characteristics, patients will undergo a multidimensional evaluation. This will include the functional status, cognitive functioning, perceived HRQoL and psychological aspects. All patients will be also asked to report any prior experience in using technological devices during rehabilitation. Moreover, the same information will be collected from the therapists involved, along with their individual socio-demographic and occupation-related data (i.e., age, gender, occupation, and overall seniority).

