### 2.6 Statistical analyses

Descriptive statistics will be conducted on participants’ socio-demographic and clinical characteristics, functional status, cognitive functioning, and HRQoL, and psychological status. Explorative analyses will be then conducted to estimate pre- post-treatment changes and long-term effects concerning the multidimensional evaluation performed. Particularly, these will be carried out by comparing patients who share the same medical disease and who experienced the use of the same technological device during rehabilitation. Within- and between-group pre- post-intervention differences will be tested with the paired-samples *t*-test and independent samples *t*-test, respectively. Additionally, a repeated-measures ANOVA test will be used to assess the longitudinal trajectories. Regarding technology evaluation, descriptive statistics will be conducted on devices usability, experience of use and psychosocial impact. Furthermore, post-hoc analyses will be performed to estimate the differences on technology evaluation in relation to the clinical condition and severity of participants. As for therapists’ devices experience of use, the semi-structured interviews will be analysed through inductive thematic analysis [73]. In conclusion, association analyses (e.g., correlations, regressions) will be carried out to explore the inter-relationships among all the variables measured. The Statistical Package for the Social Sciences (SPSS, version 28.0) will be implemented for data analyses. Sample size adequacy was estimated by resorting to power analysis [74], using G*Power Software Version 3.1.9.7 [75] on a repeated-measures ANOVA (within-between interaction) with three measurements, two groups, and a correlation among repeated measures of 0.5 (power: 0.80; α = 0.05). The required sample size to detect small-medium effect sizes (f = 0.20) was a minimum of 42 patients.

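### Time since injury, stroke or surgery is neither restricted at entry nor among the listed data, so if the non-randomised arms differ in it, natural recovery would bias the 4-week comparison and the listed data could correct this only in part

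*Protocol article*

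**What the plan says.** All references are to the protocol article.

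- **Timing of baseline (section 2.1).** "At hospital admission (or after clinical stabilization), patients will be screened according to the criteria described above". Eligible patients then have the baseline evaluation. No limit is put on how long after the event either point may fall.
- **Eligibility (section 2.1).** The disease criterion is "diagnosis of acquired brain injury (ABI; e.g., TBI, stroke), Parkinson’s Disease (PD) or orthopaedic disease (i.e., total hip/knee arthroplasty) requiring rehabilitation intervention". It has no time-since-event window.
- **Data listed (section 2.3).** The clinical items are "clinical (i.e., BMI, primary diagnosis, comorbidities, health-related risk factors, and COVID-19-related anamnesis) characteristics". No date of injury, stroke or surgery and no disease duration appears there, and the socio-demographic list has no time variable either.
- **How the arms arise (sections 2.1 and 2.2).** "The protocol has a prospective, two-arm, open-label, non-randomized study design". "Participants will be divided into two subgroups, depending on their rehabilitation program". For the technology arm, "the intervention procedures and the related eligibility to participate will be checked according to the technology-specific guidelines and recommendations as appropriate". Programmes are also adapted to diagnosis, severity of disability and goals.
- **Analysis (section 2.6).** "Within- and between-group pre- post-intervention differences will be tested with the paired-samples" t-test within groups and the independent-samples t-test between groups, with a repeated-measures ANOVA for trajectories. Comparisons are restricted to the same disease and the same device. No covariate is named.

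**The concern.** After a brain injury or a joint replacement, patients improve without any device, and improve faster early than late. The gain expected over a fixed 4 weeks therefore depends on where on that curve the baseline falls. Here baseline can fall anywhere on it, and restricting to one disease and one device does not align patients by recovery stage.

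The arms are formed by programme and device eligibility, both of which could plausibly follow recovery stage. If they do, the arm seen earlier gains more even when the devices do nothing.

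This is partly a data-collection problem and not only a choice of model, because a later decision to adjust can use only what was recorded. The baseline score is an incomplete substitute for the date. A low score may mean an early patient with much recovery ahead, or a late patient near a poor plateau, and the two have different expected gains.

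**Working it through.** **1. The plan's own figure.** Section 2.6 gives N = 42 for a within-between interaction with f = 0.20, three measurements, two groups, correlation 0.5, power 0.80 and α = 0.05. With λ = N·f²·3/(1 − 0.5), df1 = 2 and df2 = 2(N − 2), power is 0.793 at N = 41 and 0.803 at N = 42. The figure reproduces, and an equal split gives 42/2 = 21 per arm. Nothing in it bears on recovery stage.

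**2. Assumed inputs, none from the article.** The score at t weeks after the event is plateau − D·exp(−t/τ) + error. D has mean 1.5 (SD 0.5), plateau SD is 0.8 and error SD is 0.5. Time since event is gamma-distributed, τ is 4 to 10 weeks, and there is no device effect. On this scale the baseline score has SD close to 1.

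**3. Expected bias.** The expected 4-week gain is 1.5·(1 − exp(−4/τ))·E[exp(−t/τ)]. For gamma time with mean m and shape k, E[exp(−t/τ)] = (1 + m/(kτ))^(−k). With k = 4:

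- τ = 4, means 3 and 6 weeks: 0.948 × (0.503 − 0.280) = 0.21
- τ = 6, means 3 and 6 weeks: 0.730 × (0.624 − 0.410) = 0.16
- τ = 10, means 3 and 5 weeks: 0.495 × (0.749 − 0.624) = 0.06

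With k = 2 the first line becomes 0.948 × (0.529 − 0.327) = 0.19.

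**4. Simulation, 3000 replicates per setting, 21 per arm.** Each cell gives bias in SD, then type I error.

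| Setting | t-test on change | adjusted for baseline score | adjusted for baseline score and log time |
|---|---|---|---|
| τ = 4, 3 vs 6 weeks | 0.21, 15% | 0.10, 7% | 0.01, 5% |
| τ = 6, 3 vs 6 weeks | 0.16, 11% | 0.06, 6% | 0.01, 5% |
| τ = 10, 3 vs 5 weeks | 0.06, 5.5% | 0.01, 5% | 0.00, 5% |

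With equal timing in both arms, bias is nil.

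**5. Cross-check of the type I error.** The error part of the SD of change is √2 × 0.5 = 0.71, so 0.21 is about 0.21/0.71 = 0.30 SD of change. The noncentral t with 40 df and noncentrality 0.30 × √(21/2) = 0.97 rejects 15.8% of the time, close to the simulated 15%. The simulated figure is slightly lower because recovery also varies between patients.

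**6. A second set of assumptions.** Recoverable deficit 40 points, τ = 6 weeks, between-patient SD 12, measurement SD 8, mean time since event about 4 weeks in the earlier arm, 21 per arm.

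| Gap between arms | unadjusted | adjusted for baseline score | also adjusted for time since event |
|---|---|---|---|
| 1 week | 1.6 points, 7.9% | 0.5, 5.8% | 0.1, about 5% |
| 2 weeks | 3.1 points, 13.8% | 1.1, 6.7% | 0.3, about 5% |
| 3 weeks | 4.1 points, 20.9% | 1.2, 6.3% | 0.1, about 5% |

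Here the baseline score leaves about a third of the bias (for example 1.1/3.1 = 35%).

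**7. Smaller comparisons.** Section 2.6 compares within disease and device. Spreading the minimum of 42 evenly over three diseases and two arms gives 42/6 = 7 per arm, before any split by the six devices. At 7 per arm, type I error is about 5% to 8% unadjusted and 5% to 6% with the baseline score. The bias in SD is unchanged.

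**The case against.** A reader might infer that the arms will show a false difference. The article does not support that. The stabilization clause applies to all patients alike, and nothing ties a late baseline to one arm. The device guidelines are cited, not shown. So neither a gap nor its direction is established.

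A reader might also infer that the date is certainly not collected. That too goes further than the text. The clinical list is introduced by 'i.e.', but the article uses 'i.e.' loosely. Cognitive functioning is given a shorter 'i.e.' list in the abstract than in section 2.1, and severity is to be analysed in section 2.6 although the list in section 2.3 has no severity item. The full protocol or case report form may hold the dates.

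The larger figures, 0.21 SD and 15%, belong to the unadjusted test. What is specific to the missing date is the bias left after adjusting for the baseline score, and that is small. The curve is assumed for a motor-type score. Much of the battery concerns quality of life, mood and device experience, and Parkinson's disease has no index event. Section 2.6 calls the analyses explorative, and section 3.1 concedes the lack of randomisation and calls the results preliminary.

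All of this limits the size and certainty of the point without removing it. Section 3.1 does not mention recovery stage. The analysis actually stated is the unadjusted one, so the larger figures are the ones that would apply to it if a gap exists. If the dates are already on file, the remedy is cheaper still.

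**Conclusion.** The point holds as a conditional one, for brain injury and arthroplasty only. The article sets no time-since-event window, lists no date from which to derive that time, and compares change between non-randomised arms with no named covariate. If the arms differ by 2 to 3 weeks in mean time since event, the 4-week difference would carry a bias of about 0.06 to 0.21 SD as planned, and about 0.01 to 0.10 SD after adjusting for the baseline score. Type I error at 21 per arm is then about 5.5% to 15% and about 5% to 7% respectively. Smaller per-disease, per-device comparisons lower the type I inflation but not the bias. These sizes rest on assumed exponential recovery, an assumed deficit and an assumed gap. The article does not show that a false difference will occur, or which arm it would favour.

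**What to change.** - **Record** the date of injury, stroke or surgery and the date of baseline, from the hospital record. Data collection is ongoing, so this should include patients already enrolled. If the case report form already holds these dates, say so.
- **Report** the distribution of time from event to baseline by arm within each disease, so that readers can see whether a gap exists.
- **Replace** the unadjusted between-arm comparison of 4-week change, for brain injury and arthroplasty, with a linear model that adjusts for the baseline score and log time since event.
- **For Parkinson's disease**, record disease duration and report it descriptively.

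The cost is a little chart extraction and up to two degrees of freedom per comparison. At 7 per arm the residual degrees of freedom fall from 14 − 2 = 12 to 14 − 4 = 10, which matters in very small subgroups. There the by-arm description may be the more useful part. Treatment, visits and sample size do not change.
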